## Abstract

**Background:**

Common mental disorders (CMD) are a leading cause of disability globally. Emerging evidence indicates that in low and middle income countries the treatment gap for CMD can be addressed through the use of trained and supervised lay health workers (LHWs). Few clinical trials have evaluated the use of such task-shifting approaches in sub-Saharan Africa. In Zimbabwe, we have successfully piloted a task-shifting intervention delivered by LHWs. This protocol describes a cluster randomised controlled trial to assess the effectiveness of this intervention.

**Methods:**

Each of 24 randomly selected clinics from a pool of 42 in Harare will recruit 24 participants (N = 576). The clinics are randomised in a 1:1 ratio to receive either the intervention package [a problem solving therapy package delivered over a 4–6 week period by LHWs (N = 24) followed by a 6-week group support programme which focuses mainly on teaching a craft skill] or enhanced usual care, which includes usual care and psycho-education. Primary care attenders aged 18 years and above who score positive on a locally validated CMD screening questionnaire (Shona Symptom Questionnaire, SSQ-14) will be eligible for recruitment and asked for informed consent to participate in the trial. The primary measure is the SSQ score at 6 months.

**Conclusion:**

This effectiveness trial using LHWs to address the treatment gap for CMD will contribute to the body of knowledge on the feasibility and ability for scale-up of interventions for CMD.

**Trial registration:**

PACTR201410000876178.

## Background

Common mental disorders (CMD), which include depression, anxiety and somatoform disorders, are leading causes of disease burden globally [1]. In low and middle income countries (LMIC) CMD are poorly recognised and managed resulting in a large treatment gap [2]. Low cost packages of mental health care have been recommended for settings in sub-Saharan Africa, particularly stepped care approaches to managing depression [3]. This includes provision of simple psychological interventions, which can be delivered by non-specialists [4], and referral of those who do not recover. For this to be feasible for LMIC, task-sharing approaches need to be developed due to very low numbers of mental health professionals [5]. Currently psychological interventions for depression are virtually absent in government services in most low-income African countries [3, 6].

In recent years a renewed effort to address the treatment gap through task-shifting has shown promising results in a number of LMIC [7–9]. Task-shifting involves shifting basic responsibilities to non-specialist health professionals or paraprofessionals (nurses, social and community workers) in an attempt to reduce population burden and to release specialised health resources for more complex tasks [4, 10]. There is a growing body of evidence suggesting that non-health cadres, such as LHWs, can work effectively in addressing a wide range of public health issues including mental health [11].

In Chile, low-intensity low-cost treatments for depression delivered by LHWs have been successfully integrated into primary health care [7, 12]. These types of interventions include psycho-education, components of cognitive behavioural therapy (CBT), problem solving therapy (PST) and self-help approaches [8, 9, 11]. LHWs are available and affordable and, thus, appear to be one of the most appealing cadres to incorporate in the implementation of task-shifting interventions in LMIC. However, in accordance with the World Health Organisation (WHO) guidelines, it is imperative to ensure that they receive adequate training, supervision, support, career incentives and clear job descriptions to prevent overloading of these vital resources and undermining retention rates.

In Zimbabwe, where prevalence above 20% for CMD has been reported amongst adult primary care attendees [11, 13, 14], we recently piloted a task-shifting programme called The Friendship Bench and showed evidence of the feasibility and acceptability of using LHWs to deliver a psychological intervention for CMD [11]. The Friendship Bench programme consists of a cognitive behaviour therapy (CBT) based intervention that emphasises the use of problem solving therapy (PST) for the treatment of CMD. It is delivered by trained LHWs who are employed by the city health authorities in the city of Harare, Zimbabwe. The intervention consists of six sessions of 30–45 min of structured PST, delivered in a discrete area outside of the clinic building on a bench (The Friendship Bench). The PST components consist of problem listing and identification, problem exploration, developing an action plan, implementation, and follow up. We have found preliminary evidence of a clinically meaningful improvement in CMD using this locally adapted PST approach. In a cohort (n = 320) of patients recruited at primary health care facilities the mean score of a locally validated screening tool for CMD, the Shona Symptom Questionnaire (SSQ-14) [15] fell from 11.3 (SD 1.4) before treatment to 6.5 (SD 2.4) after 3–6 sessions on the Friendship Bench [11]. However, despite these promising results, there have been no effectiveness trials of the intervention conducted to date.

This protocol describes the design of a cluster randomised controlled trial of the Friendship Bench across 24 clinics in the city of Harare’s Health Department. The study population will include all adults visiting the local clinics for HIV and non-HIV related health problems who are able to give written consent and meet study inclusion criteria.

The aim of this trial is to compare the Friendship bench intervention with an enhanced usual care component. We hypothesize that the Friendship Bench intervention will be superior to the enhanced usual care for CMD in the study population in decreasing depression severity and prevalence 6 months after treatment.

## Methods/design

Preliminary work leading to the current protocol consisted of a systematic review of psychological interventions for CMD in LMIC [16]. Further work included the identification, translation, back-translation and validation of study tools; working in partnership with the Harare City Health department to establish terms of engagement, to conduct a descriptive evaluation of all their clinics, and to administer an assessment of all 300 LHWs employed by this department through qualitative interviews with the aim of determining core competencies of this cadre. Included in the preliminary work was the development of a technological platform using cloud computing to support the LHWs through task-shifting, as well as for the collection and storage of data. Prior to this, five focus group discussions and six in-depth individual interviews were conducted with the LHWs, and six in-depth interviews were carried out with clients in order to gain their perspectives of having delivered or received the intervention. Findings from this qualitative work informed the adaptation of the intervention for the trial [17].

The intervention will be delivered by trained LHWs, supervised and supported by their existing immediate supervisors, the District Health Promotion Officers (DHPOs), who will be contacted in the event that a client presents with a red flag, such as very high scores on the assessment tool (the SSQ-14 [15]) or suicidality. The DHPOs in return will get support from the clinical psychologists and psychiatrists. All DHPOs have university education at masters level in either social sciences, public health or health promotion. The DHPOs will receive a 2 months training on CMD, use of screening tools, and will participate in the pilot trial and training of their LHWs.

### Design

The study is a cluster randomised controlled effectiveness trial with a 6-month follow-up. It will be conducted in 24 of the busiest primary care clinics, selected from the 42 clinics across Harare, Zimbabwe. All 24 clinics were eligible for selection based on a formal randomisation process attended by all City Health clinic senior staff members. Prior to randomisation, the 24 clinics were grouped into 5 strata based on HIV status, density of housing, clinic size and gender distribution of clinic users. This stratification resulted in 112,000 possible allocations for allocating clinics between the two arms in a 1:1 ratio within stratum, and of these, 3,268 allocations satisfied further criteria to ensure balance on HIV prevalence, clinic size, staff size and gender. An official public randomisation exercise facilitated by the Director of Health Services was carried out by city health staff who were not involved in the study before commencement of the trial to select one allocation. The entire study team was blinded to this exercise.

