### Sample size

The sample size of 24 clusters, each with 24 participants enrolled provides 80% power to detect an effect size of 0.75, assuming a coefficient of variation (k) = 0.2 and 20% loss to follow-up. We would have 90% power to detect this effect size if the coefficient of variation is smaller (k = 0.16), and 90% power to detect a larger effect size of 0.85 if k = 0.19. The coefficient of variation is defined as the between-cluster variation divided by the mean value, for the outcome of interest (mean SSQ score). In the absence of this measure for each clinic, we based this on the value of k for HIV prevalence. The effect size is based on a recent systematic review, which identified six intervention trials of lay-health worker (LHW) led interventions with severity of CMD as an outcome [4]. The pooled effect size for the LHW intervention vs. control at 6 months was 0.75 (95% CI 0.21–1.29) [4].

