### Data analysis

Data will be exported to Stata 13.1 for analysis. Baseline comparability will be assessed for individuals who did not consent to be part of the trial, and of participants who did not complete outcome assessments. Comparability of participants in the two arms will be assessed for potential confounding factors, notably: age, sex, HIV status and SSQ score. Due to the relatively small number of clusters, analyses will be based on cluster-level summary measures, as individual-level regression methods do not perform robustly when there are relatively few clusters per arm, especially for stratified cluster randomized trials [19]. For the primary outcome (SSQ score), the mean SSQ score for each cluster will be calculated and shown by strata and arm. The arithmetic mean and SD of these mean scores and associated 95% CI will be estimated by arm. Linear regression of the mean score on strata and arm (2-way analysis of variance (ANOVA) on arm and strata) will be used to estimate the difference in SSQ score and 95% CI associated with the intervention. For the binary outcome (proportion with depression), the risk for each cluster will be calculated, and shown by strata and arm. The mean and SD of the log risk will be used to estimate the geometric mean and associated 95% CI for each arm of the study. Linear regression of the log mean risk on strata and arm will be used to estimate the risk ratio and 95% CI. Linear regression of the mean risk on strata and arm will be used to estimate the risk difference and 95% CI. The approximate variance for the mean risks will be obtained based on the residual mean square from a 2-way ANOVA on arm and strata. A 95% CI for this will be calculated from the variance using a t-statistic with 18 degrees of freedom. Pre-defined sensitivity analyses includes adjustment for baseline SSQ score and other factors with imbalance (e.g. age, sex, HIV prevalence). We will also include tests for effect-modification by gender and other key factors.

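### The primary analysis ignores the restriction of the randomisation on four clinic factors; to the extent that these predict SSQ score within strata, its interval is too wide and its test conservative

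*Protocol article*

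**What the plan says.** The protocol article's Design section describes two layers of control over the allocation. First, "the 24 clinics were grouped into 5 strata based on HIV status, density of housing, clinic size and gender distribution of clinic users". Second, a restriction was applied within that stratification: "This stratification resulted in 112,000 possible allocations for allocating clinics between the two arms in a 1:1 ratio within stratum", of which "3,268 allocations satisfied further criteria to ensure balance on HIV prevalence, clinic size, staff size and gender". A public draw then selected one allocation from the acceptable set.

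The Data analysis section gives the primary model for the SSQ score as "Linear regression of the mean score on strata and arm (2-way analysis of variance (ANOVA) on arm and strata". For the binary outcome it spells out the error term, "based on the residual mean square from a 2-way ANOVA on arm and strata", and the reference distribution: "A 95% CI for this will be calculated from the variance using a t-statistic with 18 degrees of freedom". Those last two statements are written for the risks. The SSQ model is the same two-way ANOVA on the same 24 clinic summaries, so it has the same residual degrees of freedom.

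Covariate adjustment appears only as a secondary step: "Pre-defined sensitivity analyses includes adjustment for baseline SSQ score and other factors with imbalance (e.g. age, sex, HIV prevalence". The section mentions neither a permutation test over the acceptable allocations nor primary adjustment for the balancing factors.

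**The concern.** Restricting the draw to balanced allocations removes most of the chance between-arm difference that the balancing factors could have caused. The true sampling variance of the arm difference therefore shrinks if those factors are related to outcome. The clinic-to-clinic variation that they cause within strata is still present, though, and an ANOVA on arm and strata places it in the residual mean square. The resulting standard error describes a trial that could have drawn any of the 112,000 stratified allocations, not one of the 3,268 that were allowed.

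The stake is precision. A trial with 24 clinics has little to spare, and this one took trouble to balance on these factors. If they matter for the outcome, the stated analysis reports a wider interval than the design earned.

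The planned sensitivity analysis does not cover this. Apart from baseline SSQ score, its covariates enter when they are imbalanced, whereas the restriction keeps its own factors balanced by design. Clinic size and staff size are not among the examples it lists.

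**Working it through.** **1. The plan's own figures.** The number of 1:1 allocations is the product over strata of C(n, n/2). Five strata that total 24 clinics and give 112,000 must have sizes 2, 2, 6, 6 and 8: 2 × 2 × 20 × 20 × 70 = 112,000. The residual degrees of freedom are 24 − 5 − 1 = 18, as stated. The restriction keeps 3,268 / 112,000 = 2.9%. All three figures are coherent. They also confirm that neither the restriction nor any balancing factor enters the model.

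**2. Size of the mismatch in principle.** Let R² be the share of within-stratum variance in clinic means that the four factors explain. With 12 clinics per arm, the planned variance of the arm difference is (residual mean square) × (1/12 + 1/12). If balance were exact, the true variance would be smaller by a factor of about 1 − R². The planned standard error is then too large by about 1/√(1 − R²): 1.05 at R² = 0.10, 1.15 at 0.25 and 1.41 at 0.50.

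**3. Simulation.** All 112,000 allocations were enumerated. Four independent normal clinic factors were generated, and the 3,268 best-balanced allocations were kept, by either the largest of the four arm differences or their sum of squares. One allocation was drawn per trial, with 60,000 null trials per setting. Ranges show the two balance rules. The R² values are assumptions; the article gives none.

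| R² (assumed) | Type I error, arm + strata, 18 df | Estimated SE / true SE | Type I error with the four factors added, 14 df |
|---|---|---|---|
| 0 | 5.0% | 1.00 | 5.1% |
| 0.10 | 4.0-4.1% | 1.05-1.06 | 4.9-5.0% |
| 0.25 | 2.6% | 1.15 | 4.9-5.0% |
| 0.50 | 0.8-0.9% | 1.36-1.37 | 5.0% |

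A second simulation with the same strata gave about 4.7%, 3.9%, 3.0% and 0.8% for the planned test. A permutation test over the 3,268 set, or adjustment for the factors, stayed at 4.6-5.2%.

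**4. Power.** The true effect was set to give 80% power under stratified randomisation without restriction.

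| R² (assumed) | Planned analysis | Four factors added |
|---|---|---|
| 0 | 80% | 78% |
| 0.10 | 81% | 81% |
| 0.25 | 82% | 88% |
| 0.50 | 86% | 97% |

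**5. How large R² could be.** The Sample size section has 24 participants per clinic and 20% loss, so 24 × 0.8 = 19.2 analysed. For a within-stratum intracluster correlation ρ (also an assumption), the part of a clinic mean's variance that lies truly between clinics is ρ / [ρ + (1 − ρ)/19.2]. At ρ = 0.02 this is 0.02 / (0.02 + 0.051) = 0.28; at ρ = 0.05 it is 0.05 / (0.05 + 0.049) = 0.50. Clinic-level factors cannot explain more than that. So R² = 0.25 needs about 0.25 / 0.28 = 89% of the between-clinic variance at ρ = 0.02, or half of it at ρ = 0.05.

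**The case against.** The strongest reply is that the effect is conditional and may be small. If the four factors have no predictive value within strata, the planned test has exactly its nominal level. Three of the four (HIV, clinic size, gender) overlap with the stratifiers already in the model, and only staff size is wholly outside them. With about 19 participants per clinic and a low intracluster correlation, most of the variance in clinic means is sampling noise that balancing clinic factors does not remove. The actual balance criteria are not given either, so the best-balanced 3,268 stand in for them. All of this stands, and it is why the size can only be given as a range.

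It also stands that the error is in the safe direction. A reader might infer that the trial loses power or that its result would be unsound. The calculations do not support that: planned power is never below the stratified-only figure, and a significant result is not undermined.

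A reader might also infer an intracluster correlation of about 0.3, and hence a large effect, by combining k = 0.2 with the pilot's post-treatment mean of 6.5 and SD of 2.4: (0.2 × 6.5)² / 2.4² = 0.29. The Sample size section states no mean or SD, and it borrows k from HIV prevalence because clinic-level SSQ data were lacking. That figure should not be treated as the trial's own.

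It does not stand that the sensitivity analysis deals with the point, for the reasons given above. Nor is this a detail left to a fuller document: the article itself states the model, the error term and the degrees of freedom.

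**Conclusion.** The point holds in conditional form. The stated primary inference does not match the randomisation used, and it is conservative to the extent that the balancing factors predict 6-month SSQ score within strata. Over assumed shares of 0 to 50% of the variance in clinic means, type I error runs from about 5% down to 0.8-0.9%, with standard errors from correct to about 36% too large. The lower shares are the more plausible if the intracluster correlation is small. The cost is a precision gain left unused, roughly nil at a 10% share and about 6 points of power at 25%. It is not a validity failure. The result rests on the assumed shares, on four independent factors, and on best-balanced allocations in place of the unstated criteria. The change is worth making because it is cheap and is best fixed before outcomes are known.

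**What to change.** Pre-specify one of the following as the primary analysis, before outcome data are seen:

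- **Permutation test.** Take the stratum-adjusted difference in cluster means, refer it to its distribution over the 3,268 acceptable allocations, and obtain the confidence interval by test inversion. This matches the draw whatever the strength of the factors. The set is large enough: if the criteria treat the arms symmetrically, the smallest two-sided p-value is 2 / 3,268 = 0.0006.
- **Covariate adjustment.** Add the balancing factors, or a pre-named few of them, to the primary cluster-level regression, and reduce the degrees of freedom by the number added.

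In either case, keep the 18-df ANOVA on arm and strata as a supportive analysis, and apply the same choice to the binary outcome.

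The permutation route costs a short program, and regenerating the list of allocations if it was not kept (the article reports only the count). The covariate route costs up to 4 degrees of freedom (critical t from 2.10 to 2.14) and about 2 points of power if the factors prove not to be prognostic.

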### Setting

The study is being conducted in Harare, Zimbabwe. As of 2014 there were 42 primary health care clinics in operation around Harare with each one catering for 20,000–80,000 people, from the most socio-economically disadvantaged sectors of the population.

### Recruitment procedure

All adult persons attending primary health care facilities will be sensitised verbally by a study team member who will initially inform all those waiting to be seen on the day about the study by explaining what common mental disorders are and how they can affect existing medical conditions such as hypertension, HIV, TB, diabetes. After the verbal sensitisation procedure patients will be allocated a computer generated random number corresponding to their position in the waiting list for the day. All those allocated the random number will be invited for a more detailed talk about the study before being invited to participate in the next stage of the recruitment. Those showing interest will immediately be screened and assessed for study eligibility as described below.

### Screening and assessment instruments

Common mental disorders (CMD) will be measured by the SSQ-14 which has been used extensively in Zimbabwe as a screening tool with reliable sensitivity and specificity [15]. The SSQ-14 is a dichotomous 14-item questionnaire which will be administered by a research assistant who is blinded. The SSQ-14 is a tool for detecting CMD used largely at primary health care settings in Zimbabwe. Until recently the cut-off score for this tool was 8/14, however, following the re-validation of this tool in an HIV setting the cut-off score has been raised to 9/14. The SSQ-14 will be the primary outcome measure for CMD at 6 months after recruitment.Clinical diagnosis of depression will be measured by the Patient Health Questionnaire (PHQ-9).

The PHQ-9 is a 9-item Likert scale which is used to make a diagnosis of depression [18]. This tool has recently been validated in Zimbabwe and the cut-off score for severe depression has been set at 20/27 following the piloting of the tool amongst patients utilising primary health care facilities. The PHQ-9 will be used to screen for depression and establish severity of symptoms in all participants who score above 11 on the SSQ-14 as a way of confirming red flags (suicidal cases) and the need to refer to the next level of care. Furthermore, it will be used as a secondary outcome measure for depression at 6 months because the SSQ-14 is not a specific measure for depression. All participants in the intervention arm scoring ≥20 on the PHQ-9 will be immediately referred to a clinical psychologist for further assessment. Participants referred for further care will not be excluded from the study but will receive the extra input from either a psychiatrist or clinical psychologist in addition to the PST, while in the control arm individuals will be referred to a tertiary facility offering psychiatric services as part of standard care in the event that the clinic staff are unable to manage the cases. Depression as defined by the PHQ-9 using a cut point of 11 and above for caseness [18] at 6 months after entering the trial will be our secondary outcome measure.

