### Inclusion criteria

All persons residing in the area in possession of a valid national identification card attending the local clinics who are aged 18 and above and are able to give written informed consent will be eligible for enrolment if they score above the pre-determined cut-off point (≥9) on the SSQ-14 [15].

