Remember	**Action plan: (**G) Zero in on a specific solution, focus on what client wants to do and *not what you think should be done*, (H) How, when, what assistance is needed? Referral if necessary (I). Identify activities the person used to find rewarding and which matter to them and encourage these (J), **Implementation:** (K) How will it be done? Motivate; homework, Refer after 4th session to support group. **Follow up: (**L) What has been achieved? What were/are the obstacles if any? Go back to Part 1 as often as needed during the 6 sessions (M) Reinforce. What has been achieved, repeat SSQ score. (N) No improvement refer to supervisor. nurse counsellor
Tools	SSQ-14, Friendship bench manual, referral protocol
Supervision	Weekly group supervision by a clinician (Psychologist) or senior study team member trained in PST. Access to direct mobile voice call to support team

LHWs will receive supervision and support from the clinical team at site level or through mobile phones using voice calls, and where necessary SMS messaging. The supervision will be for critical cases such as those with suicidal ideation who may need the input of a psychiatrist/psychologist and or medication. The SMS messaging/voice call will also be sent by the LHW to the participant particularly in cases where a participant has not turned up for a session on the bench and where challenges such as being unable to contact participant are encountered the project coordinators with the LHW will follow up with a voice call and if this yields no results a physical home visit will be carried out by the two. The support structure is based on a pre-determined algorithm developed during the formative research. This consists of study screen tool cut-off scores, criteria for referral including assessment for “red flags” clients who are suicidal and procedure immediate referral to a tertiary facility.

The control group will receive enhanced usual care (EUC) care through the clinic which will include psychoeducation on CMD, medication if indicated and/or referral to a psychiatric facility as part of usual standard procedure when clinic staff are unable to manage serious CMD cases. Participants will also receive between 2 and 3 supportive SMS messages or voice calls with the last SMS message or voice call being a reminder to attend the 6-months assessment.

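### The screening PHQ-9 is tied to SSQ-14 scores above 11 although entry is at 9, so about half of entrants lack a baseline on the secondary-outcome instrument

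*Protocol article*

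**What the plan says.** All places are in the Protocol article, under Methods/design unless stated.

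- **Entry.** Under Inclusion criteria, persons "will be eligible for enrolment if they score above the pre-determined cut-off point (≥9) on the SSQ-14".
- **Screening PHQ-9.** Under Screening and assessment instruments, the PHQ-9 is "used to screen for depression and establish severity of symptoms in all participants who score above 11 on the SSQ-14". Its purpose at this stage is to confirm red flags and to establish whether referral onward is needed.
- **Referral threshold.** The same section states: "All participants in the intervention arm scoring ≥20 on the PHQ-9 will be immediately referred to a clinical psychologist for further assessment". In the control arm, referral to a tertiary facility depends on whether clinic staff can manage the case. No PHQ-9 threshold is given there.
- **Secondary outcome.** Depression at 6 months is PHQ-9 caseness at a cut point of 11. The reason given for using the PHQ-9 is "because the SSQ-14 is not a specific measure for depression".
- **Hypothesis.** The Background expects superiority "in decreasing depression severity and prevalence 6 months after treatment".
- **Baseline factors.** Data analysis names age, sex, HIV status and SSQ score for comparison between arms, and pre-defines a sensitivity adjustment for baseline SSQ score and other imbalanced factors. PHQ-9 is not named.
- **Later routes in the intervention arm.** Table 1 lists the tools as "SSQ-14, Friendship bench manual, referral protocol" and includes a step to "repeat SSQ score. (N) No improvement refer to supervisor". The Intervention section adds support from supervisors and psychologists, weekly supervision, and clinicians' review of session recordings.

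**The concern.** The entry rule and the PHQ-9 rule use different SSQ-14 thresholds, and nothing in the article covers the scores between them. This matters in two ways.

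1. **Baseline of the secondary outcome.** In both arms, those entering at 9 to 11 have no baseline PHQ-9. The arms can then be compared at baseline on that instrument only among those above 11, and change in depression on its own scale can be described only in that subgroup. A baseline check on the outcome's own scale is useful here: there are only 24 clusters, and the Discussion says that the unblinded study coordinators take part in recruitment.
2. **Referral at entry.** The intervention arm has a fixed action at PHQ-9 of 20 or more. It cannot operate at entry for a participant whose PHQ-9 is not taken. The next PHQ-9 described is at 6 months, well after the 4–6 week therapy.

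**Working it through.** **Step 1: the scores that fall between the rules.** Entry is at 9 or more on a 14-point scale, so the admissible scores are 9, 10, 11, 12, 13 and 14. The PHQ-9 rule covers 12, 13 and 14. Three of the six scores (9, 10, 11) are outside it.

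**Step 2: inputs for the size.**
- Pilot SSQ-14 before treatment: mean 11.3, SD 1.4, n = 320 (Background).
- Planned sample: 24 clinics × 24 = 576 (Abstract, Methods). With 1:1 allocation, 12 × 24 = 288 per arm.
- Assumption: trial entrants resemble the pilot cohort. The article gives no score distribution for the trial and states no figure for this share, so there is nothing to reproduce.

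**Step 3: normal approximation on whole scores.** Each score s takes the interval s ± 0.5, and the distribution is restricted to 9–14:

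P(9–11) = [Φ((11.5 − 11.3)/1.4) − Φ((8.5 − 11.3)/1.4)] / [Φ((14.5 − 11.3)/1.4) − Φ((8.5 − 11.3)/1.4)]

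= [Φ(0.143) − Φ(−2.000)] / [Φ(2.286) − Φ(−2.000)]

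= (0.5568 − 0.0228) / (0.9889 − 0.0228) = 0.5340 / 0.9661 = **0.553**

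- Intervention arm: 0.553 × 288 = 159
- Both arms: 0.553 × 576 = 318
- Per clinic: 0.553 × 24 = 13

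**Step 4: sensitivity.**

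| Assumption | Share at 9–11 | Of 288 |
|---|---|---|
| Mean 11.3, SD 1.4 | 55% | 159 |
| Mean 10.8 (assumed), SD 1.4 | 68% | 195 |
| Mean 11.8 (assumed), SD 1.4 | 42% | 121 |
| Mean 11.3, SD 1.2 (assumed) | 56% | 162 |
| Mean 11.3, SD 1.6 (assumed) | 54% | 157 |
| Pilot entered at 8 (assumed), only 9 or more kept | 54% | 155 |

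If the score is treated as continuous, with no half-point correction, the pilot values give about 40%. That suits a whole-number score less well.

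**Step 5: bounds without a shape.** Take all distributions on 9–14 with mean 11.3 and variance 1.4² = 1.96, and minimise or maximise P(9–11) by linear programming.
- Minimum 0.257 (mass 0.257 at 9, 0.708 at 12, 0.035 at 14): 0.257 × 288 = 74; 6 per clinic.
- Maximum 0.823 (mass 0.115 at 9, 0.708 at 11, 0.177 at 14): 0.823 × 288 = 237; 20 per clinic.

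**Step 6: what cannot be computed.** The article gives no joint SSQ-14 and PHQ-9 data. The number scoring 9–11 on the SSQ-14 and 20 or more on the PHQ-9 cannot be estimated from it.

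**The case against.** - **Two-stage triage is a legitimate design, and no harm is shown.** This stands. The count in the working is of people without a PHQ-9, not of missed severe cases, which could be few.
- **The rule does not say that nobody else gets a PHQ-9.** The section also says, without restriction, that the PHQ-9 measures the clinical diagnosis of depression, the referral rule speaks of all intervention participants, and the list of baseline factors is not exhaustive. This stands in part. But a rule that names a subgroup by a threshold is naturally read as limited to it, and no sentence gives those at 9–11 a PHQ-9 before 6 months.
- **A reader might infer that the stated reason for the PHQ-9 outcome, "because the SSQ-14 is not a specific measure for depression", shows the gate misses severe depression.** The article does not support this. The phrase explains the choice of the 6-month outcome. It speaks to specificity, whereas a gate misses cases through poor sensitivity.
- **Other protection exists and is not all SSQ-based.** This stands. Suicidal intent is an exclusion, and suicidality triggers escalation. Lay health workers can call on supervisors and psychologists, supervision is weekly, and clinicians review recordings. The referral algorithm is not shown, so the PHQ-9 cannot be said to be absent from it.
- **The hypothesis is a contrast between arms and needs no baseline PHQ-9.** This stands for validity. Everyone has a baseline SSQ-14, and adjustment for it is planned. A complete baseline PHQ-9 would add a balance check and an adjustment on the outcome's own scale.
- **Wider measurement may add specialist care in one arm only.** This is a real cost, taken up in the fix.

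**Conclusion.** The concern holds as a modest, cheaply corrected weakness. As written, about half of entrants (55% under the pilot distribution; 26% to 82% with only the pilot mean and SD fixed) have no baseline value on the secondary-outcome instrument. Those in the intervention arm cannot trigger the PHQ-9 referral at entry. The figures assume that the trial's entrants resemble the pilot cohort.

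A reader might go further and conclude that severely depressed participants are left without safeguards, or that the depression outcome is compromised. Neither follows. The number at 20 or more among those at 9–11 is unknown, suicidality and clinical concern have their own routes, and the primary analysis and the 6-month comparison between arms remain valid.

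**What to change.** **Screening and assessment instruments:** remove the restriction to SSQ-14 scores above 11 and give the PHQ-9 at recruitment to every enrolled participant in both arms. Keep the existing referral rules in each arm. If the full protocol already does this, correct the article's wording.

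**Data analysis:** add baseline PHQ-9 to the factors compared between arms and to the pre-defined sensitivity adjustment for the 6-month depression outcome.

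**Control arm:** make participants newly found at 20 or more known to clinic staff, under the existing standard-care route.

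**Cost:** about 318 extra nine-item questionnaires, or 13 per clinic (6 to 20 under the shape-free bounds). The tool is locally validated and already in use in the trial. Some additional specialist referrals in the intervention arm are possible. Their number cannot be predicted from the article, so referrals should be reported by arm to let readers judge how much specialist care accompanied the lay-worker therapy.
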